#### Tumor microenvironment proteomic analysis

FFPE tissue samples will be obtained from diagnostic biopsies or resection specimens naive of treatment. Proteomic analyses will be performed after all needed determinations for diagnosis and clinical management have been conducted. Proteomic analyses will be conducted in the Proteomics unit of Navarrabiomed (ISO9001:2015 certified). Samples will undergo "in-gel" digestion, peptide reconstitution, and purification before identification by liquid chromatography-tandem mass spectrometry (LC–MS/MS), using the Ultimate 3000 RSLCnano system coupled with an Orbitrap Exploris 480 mass spectrometer (Thermo Fisher Scientific). Spectra resulting from the analysis will be processed using MaxQuant software and compared with the most updated *H.sapiens* reference proteome from the UniProt database.

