Some studies have assessed differential clinical and molecular characteristics of EOGIC, proposing the recognition of a novel entity with special requirements for diagnosis and clinical management. EOGIC usually presents in advanced clinical stages and with aggressive phenotypes, including poor differentiation, signet ring histology and vascular-perineural invasion [17]. EOCRC typically occurs in the distal colon and rectum, with a higher proportion of microsatellite unstable tumors, fewer cases of mutations in *APC*, *KRAS*, and *BRAF*^V600E^, and mostly with a molecular subtype related to infiltration of inmune cells [18–20]. Interestingly, it has been linked to a distinctive microbiota [21]. EOGEC commonly associates with atrophic gastritis from autoinmune phenomenons. It presents higher tumor grades, higher proportion of poorly cohesive histology and signet-ring cell subtype, with an increment of CDH1 mutations, as well as the molecular subtype EBV (TCGA classification) [20, 22]. Early onset pancreatic cancer has lower proportion of *KRAS*, while *SMAD4* mutations are more frequent. Different signaling pathways like Hedgehod, TGFβ, hypoxia or PI3K/AKT have also been reported in these patients [23, 24].

Additionally, EOGIC patients have distinctive characteristics that affect their clinical management. Due to their extended life expectancy, they face long-term effects from therapeutic strategies, which may impact their quality of life and more specifically their sexual and reproductive health. Furthermore, cancer diagnosis at a young age normally represents a more pronounced psychological disorder derived from its impact on professional, social and familiar commitments. This is why it is essential to treat these patients individually, considering all these factors and providing a more personalized and precise approach [6, 25–30].

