### Patient selection and recruitment

Patients will be selected and recruited in routine medical appointments by specialized medical oncologists at the participating Hospitals during the period of 01/2024–12/2025. Patients will be included consecutively based on inclusion and exclusion criteria, following a ratio of 1 EOGIC: 2 non-EOGIC.

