#### Inclusion criteria

Patients with newly diagnosed, histologically confirmed colorectal adenocarcinoma (CRC, group A), gastroesophageal adenocarcinoma (GEC, group B) and pancreatic adenocarcinoma (PC, group C).Age 18–50 (both included) years old for the EOGIC group, and 60–75 (both included) years old for the non-EOGIC group.

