#### Exclusion criteria

Eastern Cooperative Oncology Group (ECOG) performance status of ≥ 3.Presence of comorbidities which may compromise participation of the patient in the study (mainly in terms of capability to complete the questionnaires).Having received oncological treatment directed at the newly diagnosed cancer (i.e., at the time of inclusion the patient has not yet started any type of treatment, including surgery).

Although there is a lack of consensus in the age threshold to define EOGIC, it is generally set at 50 years old, in agreement with the initiation of most of the screening programs [6]. Regarding the non-EOGIC group, we set the lower age at 60 years old, in order to ensure a clear differentiation between groups; while the upper limit is established at 75 years old in order to exclude the very elderly population. Again, although the lack of consensus in the age to define elderly patients, several studies in the field consider 75 years old as the lower limit to define this population, and present evidence on their differential characteristics compared to on-average patients [32–36]. Age range is also defined with the objective to minimize age related confounding effect.

We estimate the following number of patients to be included in each group: CRC-group A, 40 EOGIC and 80 non-EOGIC; GEC- group B, 20 EOGIC, 40 non-EOGIC; PC-group C, 20 EOGIC, 40 non-EOGIC (Fig. 1a). Estimated number of patients has been calculated based on incidence of EOGIC in HUN in the years 2019–2022 (Fig. 1b), and assuming a similar incidence in the other participating hospitals, taking into account that all participating Hospitals cover a similar target population. The rate of patient inclusion will be evaluated periodically and if necessary, recruitment period will be extended or additional Hospitals of the geographical area will be invited to participate in the study in order to increase patient recruitment.

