**Fig. 1 Fig1:**
[figure not shown]
Estimated patient recruitment. **a** Diagram of the recruiting centers and estimated number of patients to be recruited by group. **b** Number of cases with GI cancer treated in Medical Oncology Unit of the HUN in the years 2019–2022. Red depicts EOGIC, while green depicts non-EOGIC (age > 50 years) CRC: colorectal cancer; EOGIC: early onset gastrointestinal cancer. GEC: gastroesophageal cancer; PC: pancreatic cancer

As aforementioned, patients will be included in a ratio of 1 EOGIC: 2 non-EOGIC with the aim of increasing sample-size in the control group, thus optimizing statistical analyses and ensuring study viability. Assuming a statistical power of 80% and a significance level of 5%, this sample size allows for the detection of statistically significant differences between the EOGIC and the non-EOGIC group in an exploratory approach. For continuous variables at a Cohen´s d of 0.385-medium size effect; and for categorical variables, with variables at a 10% prevalence in the non-EOGIC group, a15% of size-difference between groups; with variables at a 30–70% prevalence in the non-EOGIC group, a 20% difference between groups. Additionally, semi-supervised automatic learning will be employed for pan-tumor comparisons, a sample size of 60 EOGIC and 140 non-EOGIC patients is necessary to detect differences in an interest cluster of 20%.

This study is in agreement with international, national and local regulations for clinical studies (latest version of the Declaration of Helsinki, The Spanish Law for Biomedical Research and local regulations “Normas de Buena Práctica Clínica y Orden Foral 125/2009) as well as personal data protection (General Data Protection Regulation (RGPD-Regulation (EU) 2016/679), Spanish Organic Law 3/2018 and the local regulation “Resolution 1387–2017 of the Managing Director of the SNS-O”). Ethics Committee for Investigation with medicinal products from Navarra, have approved this project and a unified informed consent and patient-information sheet has been developed following guidelines of the Spanish Medication and Sanitary Product Agency (AEMPS). Previous to the inclusion, informed consent will be obtained for each patient.

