#### Histopathological data and tissue proteome

General histopathological and molecular characteristics of the tumor will be comprehensively studied, via specific determinations relevant for each of the etiologies.

General histopathological characteristics, tumor location and clinical tumor stage will be recorded. Colorectal and gastroesophageal cancer staging will be assessed according to The Eighth Edition AJCC Cancer Staging Manual [39]. Pancreatic cancer will be classified as resectable, borderline resectable, locally advanced unresectable and metastasic. Number of metastasic sites and their location will also be recorded in stage IV of the disease. Histology type and differentiation grade will be assessed in formalin-fixed paraffin-embedded (FFPE) tissue. Molecular characteristics to be recorded in FFPE tissue include MMR/MSI status by immunohistochemical analysis of mismatch-repair proteins (*MLH1, MSH2, MSH6*, and *PMS2*) as well as CD3 and CD8 infiltration in all tumors. Additional molecular characteristics will also be measured according to tumor type: *HER2* amplification status, *KRAS*, *NRAS* and *BRAF* mutations for CRC; *HER2* overexpression/amplification status, PDL1 (CPS) and CLDN 18.2 and FGFR2b expression for GEC; and *KRAS* mutations for PC. For all tumors, Next-Generation Sequencing (NGS) analyses targeting cancer-related genes will be performed if a suitable sample is available.

Histopathological characteristics will be preferentially assessed in the recruitment center. If available after routine determinations for diagnosis and clinical management, FFPE tissue samples will be sent to the Pathology Department of HUN in order to perform a centralized assessment of missing determinations.

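### Tissue proteomics pools biopsies and resection specimens without restriction or adjustment, so any group difference in specimen mix can appear as an EOGIC signature

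*Protocol article*

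**What the plan says.** All of this is in the protocol article.

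- **Specimen source** (Tumor microenvironment proteomic analysis): "FFPE tissue samples will be obtained from diagnostic biopsies or resection specimens naive of treatment". No order of preference is given, and no matching or stratification by specimen type.
- **Leftover tissue** (same section): "Proteomic analyses will be performed after all needed determinations for diagnosis and clinical management have been conducted".
- **Stage at presentation** (Background): "EOGIC usually presents in advanced clinical stages and with aggressive phenotypes". No percentage is given.
- **Recruitment** (Patient selection and recruitment): "Patients will be included consecutively based on inclusion and exclusion criteria, following a ratio of 1 EOGIC: 2 non-EOGIC". Stage is not a matching factor.
- **Stage data** (Histopathological data and tissue proteome): "General histopathological characteristics, tumor location and clinical tumor stage will be recorded". The Statistical analyses section does not name stage as an adjustment factor.
- **Planned sizes** (end of Exclusion criteria): "CRC-group A, 40 EOGIC and 80 non-EOGIC; GEC- group B, 20 EOGIC, 40 non-EOGIC; PC-group C, 20 EOGIC, 40 non-EOGIC", which sum to 80 v 160.
- **Signature tests** (Statistical analyses): the t-test or Mann-Whitney test already listed for continuous variables, with a multiplicity correction such as FDR. The machine-learning step is described as a way to find patient clusters, not as an adjustment.

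**The concern.** A resection specimen free of prior treatment is available only when surgery comes first. Patients with metastatic disease, or given neoadjuvant treatment, can supply only a biopsy. Specimen type therefore follows stage and treatment pathway, and the article itself links stage to age group.

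A small biopsy, a biopsy of a metastasis and a resection block can hold different proportions of tumour, stroma, normal tissue and blood. A bulk microenvironment proteome reflects those proportions. If the mix differs between the groups, a protein that differs only by specimen type will also differ by age group in an unadjusted test. FDR limits chance findings among many tests. It does nothing about a systematic difference that is really present in the data but comes from the specimen.

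At stake is the list of proteins carried forward from this study as candidate therapeutic targets.

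**Working it through.** **1. The plan's own figure.** Detectable standardised difference at 80% power and two-sided 5% (sidedness is not stated; two-sided assumed), 80 v 160:

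d = (1.960 + 0.842) × √(1/80 + 1/160) = 2.802 × 0.1369 = 0.384.

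The exact noncentral t calculation gives 0.385, as stated in the sample-size paragraph. The stated figure is right.

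**2. False shift.** Let pE and pN be the biopsy shares in EOGIC and non-EOGIC, and D the biopsy-resection difference in within-type SDs, with no true age effect.

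- Shift: m = (pE − pN) × D
- Variance in each group: 1 + p(1 − p)D²
- z = m / √(vE/nE + vN/nN); rejection rate = Φ(z − 1.96) + Φ(−z − 1.96)

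The shares and D are assumptions; the documents give neither. For 75% v 50% and D = 1: m = 0.25, vE = 1 + 0.75 × 0.25 = 1.1875, vN = 1 + 0.5 × 0.5 = 1.25. At 80 v 160 the standard error is √(1.1875/80 + 1.25/160) = 0.1505, z = 1.66, and the rejection rate is 38%.

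**3. Rejection rate at nominal 5% for one specimen-sensitive protein** (simulated t-tests, except the 90% v 50% row, which uses the formula):

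| Biopsies, EOGIC v non-EOGIC | D (SD) | Shift (SD) | 20 v 40 | 40 v 80 | 80 v 160 |
|---|---|---|---|---|---|
| Equal | any | 0 | 5% | 5% | 5% |
| 75% v 50% | 0.5 | 0.125 | 7% | 10% | 14% |
| 75% v 50% | 1 | 0.25 | 13% | 21% | 38% |
| 40% v 60% (reversed) | 1 | −0.20 | 10% | 15% | 26% |
| 90% v 50% | 1 | 0.40 | 28% | 49% | 78% |
| 80% v 40% | 1.5 | 0.60 | 42% | 72% | 95% |

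At 90% v 50%, the false shift of 0.40 within-type SD is about the size of the 0.385 effect that the study is planned to detect.

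**4. After FDR.** Further assumptions: 2,000 proteins, 20% of them specimen-sensitive, Benjamini-Hochberg at 5%, no true age effect. Mean number of falsely significant proteins, unadjusted:

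| Biopsies | D (SD) | 20 v 40 | 40 v 80 | 80 v 160 |
|---|---|---|---|---|
| 50% v 50% | 1 | not run | 0.03 | 0.03 |
| 75% v 50% | 0.5 | 0.07 | 0.13 | 0.5 |
| 75% v 50% | 1 | 0.6 | 3.2 | 16 |
| 80% v 50% | 1 | not run | 2.8 | 30 |
| 90% v 50% | 1 | not run | 24 | 170 |
| 80% v 40% | 1.5 | 24 | 144 | 349 |

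In the 75% v 50%, 1 SD row the medians are 0, 0 and 2, so the means are driven by runs in which the realised imbalance was large. Simulation noise in these means is appreciable: a repeat of that row gave 0.4, 2.5 and 18. With specimen type as a covariate, the mean stays below 0.1 in every setting run.

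**The case against.** A reader might infer from the Background that EOGIC patients will mostly supply biopsies and older patients will not. The documents do not support that. The Background sentence is a general statement without percentages. Metastatic or neoadjuvant-treated patients of any age can supply only a biopsy, so both groups may be mostly biopsies, and equal shares give no excess. The leftover-tissue rule also cuts the other way: small biopsies may be used up by routine tests, so late-stage patients may drop out of the proteome set and the imbalance could shrink or reverse. This stands against any claim about direction. It does not remove the problem, because a reversed imbalance biases too (40% v 60% in the table).

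The per-protein rates are before FDR, and FDR is in the plan. This also stands. In the 75% v 50%, 1 SD case few false proteins survive in the tumour-specific analyses. The pan-tumour figures further assume a common SD; variation between tumour types would lower them.

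A reader might also infer that the signatures are to be offered as established targets. The Discussion calls them potential targets and hypotheses that need validation, and the study describes itself as exploratory.

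Finally, block selection and model covariates often sit in a fuller protocol or analysis plan, which is not shown. That would answer a complaint about missing detail. Here, however, the article names both the mixed source and the tests, and those tests carry no covariate.

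**Conclusion.** The point holds as a conditional one. As written, the plan mixes two specimen types and compares the groups with tests that cannot separate specimen type from age group. Any imbalance in the mix, in either direction, can be reported as an EOGIC signature, and FDR does not prevent it.

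Its size cannot be derived from the documents, because it rests on assumed biopsy shares and an assumed specimen effect. Over the unequal-share cases shown, the nominal 5% rejection rate for a specimen-sensitive protein runs from 7% to 95%, and the mean number of false proteins after FDR from under 0.1 to about 350. With equal shares there is no excess. An imbalance is plausible given how naive tissue arises, but it is not established. The plan should be changed because the protection is cheap and the planned tests offer none.

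**What to change.** 1. Record specimen type in REDCap for every proteomic sample: primary biopsy, metastasis biopsy or resection.
2. In Statistical analyses, replace the unadjusted proteomic test with a linear model per protein, with group and specimen type as terms (or stratify by specimen type), and apply FDR to the group term.
3. Report the specimen mix by group, within each tumour type and overall.
4. Repeat the signature in biopsies only as a sensitivity analysis.

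**Cost.** One data field and one model term. At 75% v 50% and a 1:2 ratio, the overall biopsy share is (0.75 + 2 × 0.5)/3 = 0.583. The squared correlation of group with specimen type is (0.222 × 0.25)²/(0.222 × 0.243) = 0.057, so the variance of the group estimate rises by a factor of 1/(1 − 0.057) = 1.06. For specimen-sensitive proteins this is offset by a smaller residual variance. The biopsy-only analysis is smaller: under the same shares, 60 v 80 overall, 30 v 40 in CRC, and 15 v 20 in each of GEC and PC, so it serves as a check on direction and size of effect, not as a powered test.

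Preferring the diagnostic biopsy where enough tissue remains is optional. It would make the material more uniform, but it draws on the scarcest tissue, and a biopsy of the primary tumour is not guaranteed for every patient.

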#### Statistical analyses

Descriptive and comparative analyses will be performed separately for each type of tumor: CRC (Group A), GEC (Group B), and PC (Group C) as well as at a pan-tumor level, comparing all EOGIC to non-EOGIC patients.

Population characteristics will be described using measures of central tendency and dispersion for continuous variables and frequencies and percentages for categorical variables. Normality of the sample will be analyzed for continuous variables through histogram exploration, the Shapiro–Wilk test, and homoscedasticity by Levene's test. Group comparisons will be made using Student's t-test or Mann–Whitney U test for continuous variables and Pearson's Chi-square test or Fisher's exact test for categorical variables. Correlation between different measurements and conditions of interest will be assessed using Pearson's or Spearman's correlation tests.

Analyses for circulating inflammatory proteins, the microbiota and the tumor microenvironment proteome, will be conducted utilizing specialized software for each application. Raw data will be processed, applying quality criteria, and differential signatures between groups will be identified. For signature identification, previously mentioned tests, including correction methods for multiple comparisons such as the false discovery rate (FDR).

For pan-tumor and gender/sex-level comparisons, machine learning algorithms will be used, allowing integration of all patient clinical and lifestyle profile data with variables derived from circulating inflammatory proteins, microbiome and tumor microenvironment proteome profiles, identifying clusters of patients with similar patterns.

Statistical analysis will be performed using IBM Statistical Package for the Social Sciences (SPSS) version 24.0, GraphPad Prism v9, and R 4.1.0 (R Foundation for Statistical Computing, Vienna, Austria. http://www.R-project.org/).

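### Tissue for the proteome and CD3/CD8 comparisons is not restricted, stratified or labelled by anatomical site, so an unequal share of metastasis blocks could pass for an EOGIC signature

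*Protocol article*

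**What the plan says.** All references are to the protocol article.

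- **Tissue source** (Tumor microenvironment proteomic analysis): "FFPE tissue samples will be obtained from diagnostic biopsies or resection specimens naive of treatment". The rule covers treatment status and specimen type, not anatomical site.
- **Immune infiltrate** (Histopathological data and tissue proteome): FFPE determinations include mismatch-repair status "as well as CD3 and CD8 infiltration in all tumors". No site rule is given.
- **Stage** (Inclusion criteria, Exclusion criteria): no stage limit is set, and histological confirmation need not come from the primary. The histopathology section includes a metastatic category for pancreatic cancer and says "Number of metastasic sites and their location will also be recorded in stage IV of the disease". Tumour location and metastasis location are therefore listed, but the origin of the analysed block is not.
- **Expected imbalance** (Background): "EOGIC usually presents in advanced clinical stages and with aggressive phenotypes".
- **Analysis** (Statistical analyses): "Group comparisons will be made using Student's t-test or Mann–Whitney U test for continuous variables". For the omics layers, "Raw data will be processed, applying quality criteria, and differential signatures between groups will be identified", using the same tests with a multiplicity correction such as FDR. This is done per tumour type and pan-tumour. No restriction, stratum or covariate for sampling site or stage is described.

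**The concern.** A block from a liver, peritoneal or nodal metastasis contains that organ's own proteins and resident immune cells. If such blocks are a larger fraction of one age group, sampled organ is confounded with age group, and a two-group test cannot tell them apart.

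The 1:2 ratio is planned within each tumour type (40/80, 20/40, 20/40), so the organ of the primary is balanced by design in the pan-tumour comparison. Nothing balances the organ actually sampled. This is also separate from biopsy versus resection: a biopsy-only rule would leave it in place.

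FDR control limits the expected fraction of false discoveries when each test is valid under its null. Here the null is false for a reason unrelated to age at onset, so the correction does not help. Host-organ proteins would also tend to appear together and could look like a coherent biological signature. The Discussion hopes the tissue proteome will point to therapeutic targets, so follow-up work could be misdirected. Without the block's site in the data, nobody could later show whether this had happened.

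**Working it through.** **1. The plan's own figure.** With 80 EOGIC and 160 non-EOGIC, two-sided 5% and 80% power, detectable d = (1.960 + 0.842) × √(1/80 + 1/160) = 2.802 × 0.1369 = 0.384. This agrees with the stated 0.385 (power at 0.385 is 0.803), which is not in dispute.

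**2. Model for the artefact.** Let f1 and f0 be the shares of metastasis blocks in EOGIC and non-EOGIC, and D the shift of a host-organ protein in those blocks, in within-site SD. There is no true age effect.

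- Spurious difference = (f1 − f0) × D
- Variance in group i = 1 + fi(1 − fi)D²

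The documents give neither shares nor shifts. All values of f1, f0 and D are assumptions.

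**3. One case by hand.** f1 = 0.30, f0 = 0.15, D = 2:

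- difference = 0.15 × 2 = 0.30
- variances: 1 + 0.21 × 4 = 1.84 and 1 + 0.1275 × 4 = 1.51
- SE at 80 v 160 = √(1.84/80 + 1.51/160) = 0.180
- ratio = 0.30/0.180 = 1.67, so P(p < 0.05) ≈ 1 − Φ(1.96 − 1.67) ≈ 0.38
- standardised difference = 0.30/√((1.84 + 2 × 1.51)/3) = 0.24

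**4. Range.** Per-protein false-positive rate, nominal 5%, from simulation of the Mann–Whitney test, D = 2 to 4:

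| Assumed shares, EOGIC v non-EOGIC | Pan-tumour, 80 v 160 | CRC, 40 v 80 | GEC or PC, 20 v 40 |
|---|---|---|---|
| 10% v 5% | 8–11% | 6–8% | 6–7% |
| 20% v 10% | 18–25% | 12–15% | 9–13% (normal approximation) |
| 30% v 15% | 35–49% | 20–27% | 14–16% |
| 30% v 30% | about 5% | about 5% | 5% (normal approximation) |

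The t-test, which the plan also allows, is more sensitive to large shifts: 41% pan-tumour at 20% v 10% with D = 4.

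**5. One host organ only.** A liver protein shifts in liver blocks, not in nodal ones. If half of the metastasis blocks come from the organ concerned, 30% v 15% acts like 15% v 7.5% for that protein, and the pan-tumour rate falls to about 13–16%.

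**6. After FDR.** Simulated studies had 3,000 proteins, 5% of them shifted by 3 SD, independent noise, and Benjamini–Hochberg at 5%. Studies declaring at least one protein:

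- pan-tumour: about 25–50% for shares of 30% v 15% up to 50% v 30%
- CRC: about 12–17%
- GEC or PC: about 2–3%
- no imbalance: about 3–4%

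The median number declared was zero or near zero, so large mean counts come from a minority of runs.

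**7. Primary-tumour tissue only.** With f1 = f0 = 0 the bias is zero and the rate returns to 5%. Detectable d rises as blocks are dropped:

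- 20% from both groups (64 v 128): 2.802 × √(1/64 + 1/128) = 0.43
- 30% v 15% (56 v 136): 0.44
- 40% v 20% (48 v 128): 0.47

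**The case against.** **This is a condensed article.** A full protocol, laboratory manual or analysis plan may fix which block is used and log its site. That limits what can be said about fields not listed. It does not dispose of the point, because the article does state a tissue-source rule, and that rule leaves site open.

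**The imbalance is inferred.** A reader might take the Background sentence to mean that EOGIC blocks will come from metastases more often. The documents do not support that. Advanced stage is not the same as metastatic, and a metastatic patient is not necessarily biopsied at the metastasis. Both groups are recruited by medical oncologists before any treatment, which may narrow a stage gap. If nearly all blocks are primary, or the shares match, there is little or no bias. This objection stands, and it is why the conclusion is conditional.

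**The size is easily overstated.** A reader might also infer that large FDR-surviving signatures are to be expected throughout. Steps 5 and 6 show otherwise: the smaller tumour groups have too few patients, and single-organ shifts dilute the effect. The simulations also assume usable tissue from all 240 patients, although research use comes after routine determinations.

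**A primary-only main analysis has its own price.** It costs precision and removes advanced cases, possibly more of them in EOGIC, where advanced disease is held to be characteristic. This stands as well. The documents do not show that primary-only must be the sole main set.

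**The study is exploratory.** It is, and the tissue results are described as needing validation. That lowers the stakes but does not excuse a systematic bias that is cheap to detect.

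**Conclusion.** The point holds in conditional form. Following the plan as written can confound sampled organ with age group, and neither the tests nor FDR control would reveal or remove it.

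Over assumed shares of 10% v 5% to 30% v 15% and shifts of 2 to 4 SD, the per-protein false-positive rate is about 8–49% pan-tumour, 6–27% in CRC and 6–16% in GEC or PC, against 5%. It is lower where a protein shifts in one host organ only, and stays at 5% with equal shares. After FDR, the risk is mainly pan-tumour, with some in CRC and almost none in GEC or PC. These figures rest on assumed shares and shifts, the Mann–Whitney test and complete tissue. The size in the actual cohort cannot be known from the documents.

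**What to change.** 1. In the histopathology and proteomics sections, add a REDCap field for the anatomical site of each analysed block (primary or metastasis, and organ), taken from the pathology report.
2. In Statistical analyses, stratify or adjust the proteome and CD3/CD8 group comparisons by sampling site.
3. Report a primary-tumour-only analysis alongside, and call a protein an EOGIC signature only if it persists there. Say beforehand how persistence will be judged, because that set is smaller.
4. Tabulate the share of metastasis blocks by age group and tumour type, so that readers can see whether the problem arose.

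Cost: one field, some extra analysis, and less precision in the primary-only analysis (pan-tumour detectable d of about 0.43–0.47 instead of 0.38 under the exclusions assumed in step 7 of the working). Recruitment need not change.
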